#### Procedure

We will conduct semi-structured in-depth interviews with clinicians from each profession and their patients. Study 1 clinician and patient participants will be eligible to participate. We will purposefully approach individuals to provide a variety of views and perspectives, including patients who have, and who have not, been referred for imaging. Patients will be approached for an interview during the early stages of their management for low back pain so that their experience is recent. Clinicians will not be interviewed until after they complete their participation in Study 1 to avoid revealing the true nature of the study to them.

Our target sample size will be 30–45 clinicians (10–15 from each profession) and 30 patients (10 who consult each profession). Recruitment and sampling will cease once our data analysis has produced a stable set of findings and emergent codes no longer arise during data collection and analysis (i.e. once we have reached theoretical saturation) [68].

Semi-structured interviews will be conducted over the telephone by a project staff member. Interview questions will be informed by the Theoretical Domains Framework (TDF) to systematically identify barriers and facilitators to practising in accordance with best practice recommendations, focussing on the use of inappropriate imaging [69, 70]. Interviews will be audio-recorded and transcribed verbatim.

For clinician interviews, we will ask general questions about how they manage patients with a new episode of low back pain. We will ask about their knowledge of low back pain evidence-based guidelines to gain insight into the factors that hinder, or facilitate, clinical behaviour that is in accordance with the guidelines [17]. For clinicians who order imaging, we will also ask about what benefits they feel they get from imaging when they refer for it, if they feel it changes their patient management, and how they use imaging information. The interview guide will be piloted with two clinicians from each profession prior to data collection to assess its comprehensiveness, practicability and acceptability. For patient interviews we will ask about their expectations and beliefs regarding the need for imaging for their low back pain, as well as more general questions about their beliefs and attitudes about low back pain, generated from items from the Back Pain Beliefs Questionnaire [71].

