Rates of patient recruitment will be monitored via contact from the research team to clinicians and practice staff approximately every 2 weeks. We will ask participating clinicians to keep a de-identified list of patients whom they approached, and to indicate how many were ineligible and how many declined participation. To reduce the risk of selection bias, practice staff, clinicians and patients will only be told that this is an observational study on the current management of low back pain in primary care, and not that lumbar imaging is the main focus. There is a lower incidence of low back pain presentations in family medicine compared to chiropractic and physiotherapy, so patient recruitment in this setting will require more support [56].

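### Early patient interviews on imaging sit poorly with the plan's own concealment of the imaging focus, mainly because the patient's clinician may still be enrolling

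*Protocol article*

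**What the plan says.** Three statements in the protocol article bear on this.

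- **Concealment rule** (Clinician and patient recruitment): "To reduce the risk of selection bias, practice staff, clinicians and patients will only be told that this is an observational study" of current low back pain management, "and not that lumbar imaging is the main focus". The rule covers all three groups, and its stated purpose is to limit selection bias.
- **Clinician interviews** (Methods for study 2, Procedure): "Clinicians will not be interviewed until after they complete their participation in Study 1 to avoid revealing the true nature of the study to them".
- **Patient interviews** (same section): "Patients will be approached for an interview during the early stages of their management for low back pain so that their experience is recent". The interviewees come from the cohort: "Study 1 clinician and patient participants will be eligible to participate". They are chosen to include people who have and have not been referred for imaging. The interview framework is described as "focussing on the use of inappropriate imaging", and on content the section says: "For patient interviews we will ask about their expectations and beliefs regarding the need for imaging for their low back pain". More general questions about back pain beliefs are asked as well.

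The Abstract calls the qualitative study concurrent with the cohort. Encounter forms run for up to six weeks (Encounter data), and imaging is followed for 12 months (Administrative data). Each clinician enrols up to 25 consecutive patients at roughly two a month over 12 months (Clinician and patient recruitment).

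**The concern.** The plan treats an interview as something that would reveal what the study is about, and delays it for clinicians for that reason. It then interviews another group covered by the same rule early in care.

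Two routes follow. First, the interviewed patient's own imaging is still being counted, so a conversation about whether imaging is needed could alter what that patient asks for or accepts. Second, the patient goes back to a clinician who may still be enrolling. If the patient mentions the topic, the clinician could enrol or image later study patients differently. The second route is the one that touches the plan's stated purpose, because selection bias can arise only in patients who are not yet enrolled.

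The results at stake are the rate of inappropriate imaging (a primary objective) and the comparison of professions (a secondary one).

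**Working it through.** The plan gives no figure on this point to reproduce. The check is one of timing, followed by how far any disclosure could reach.

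**Timing**

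| Item | Clinicians | Patients |
|---|---|---|
| Covered by the concealment rule | Yes | Yes |
| When approached or interviewed | After Study 1 participation ends | Early in management |
| Study 1 data still accruing then | No | Yes: visits up to 6 weeks, imaging to 12 months |
| Clinician may still be enrolling then | No | Yes, except for a clinician's last enrolees |

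At two patients a month over 12 months, an early-care interview falls inside the clinician's enrolment period for most of that clinician's patients.

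**Direct reach** (inputs: 30 patient interviews, 10 per profession, from Procedure; 3750 patients from Sample size justification)

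- Share of patients: 30/3750 = 0.8%.
- Per profession, if the 3750 split equally: 10/1250 = 0.8%. Even if all ten changed status, that profession's rate would move by no more than 0.8 percentage points.

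**Indirect reach** (inputs: 175 clinicians, 50 chiropractic, 50 physiotherapy, 75 family medicine; assumption: the 30 interviewees come from 30 different clinicians)

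- Clinicians: 30/175 = 17.1%. By profession: 10/50 = 20% in chiropractic and in physiotherapy, 10/75 = 13.3% in family medicine.
- Later patients if each clinician enrols 25 and the interviewee is the first: 30 × 24 = 720, and 720/3750 = 19.2%.
- The same at the planned average of 3750/175 = 21.4 patients per clinician: 30 × 20.43 = 613, and 613/3750 = 16.3%.

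**What exposure could mean for a rate.** The documents say nothing about how clinicians would react, so the following rests on assumptions: 25% to 90% of an exposed clinician's patients enrol after the interview, the clinician's imaging rate changes by 5 to 20 points, and clusters are of equal size.

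Shift = share of clinicians exposed × share enrolled later × change in rate.

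| | Low | High |
|---|---|---|
| Chiropractic or physiotherapy | 0.20 × 0.25 × 0.05 = 0.25 points | 0.20 × 0.90 × 0.20 = 3.6 points |
| Family medicine | 0.133 × 0.25 × 0.05 = 0.17 points | 0.133 × 0.90 × 0.20 = 2.4 points |

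If clinicians in all professions reacted alike, the contrast between chiropractic and physiotherapy would not move, and either contrast with family medicine would move by at most 3.6 − 2.4 = 1.2 points. The plan aims to detect a 6-point difference between professions. The upper figures need every interviewee to disclose and every clinician to respond.

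**The case against.** The strongest reply is that concealment is already partial. Patients answer an imaging-expectation item at first and follow-up visits and two imaging-belief items at baseline (Table 1). Clinicians are asked about the usefulness of imaging, guideline knowledge, and access to and ownership of imaging (Table 2), and they record imaging on the encounter form. Only the fact that imaging is the main focus is withheld, so a patient's remark may add little. This stands as a reason to expect a modest effect. It does not remove the inconsistency: the plan delays interviews for clinicians who have already answered such items, so by its own reasoning an interview reveals more than a questionnaire.

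Other points that stand:

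- An interviewed patient is already enrolled, so the selection-bias purpose is not engaged for that patient.
- Some interviewees will already have been referred, so for them that decision precedes the interview.
- The early timing is a deliberate choice to keep experience recent. The text says when patients are approached and gives no interview date.
- A request for confidentiality may exist in a fuller protocol, so its absence from the article is not counted here. The timing, however, is stated with its reason.

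A reader might infer more than this: that concealment is broken outright, that the interview comes before most of the imaging it could change, or that the primary rate will be biased downward. The documents support none of these. They do not say when imaging falls within the 12 months, and nothing in them shows that patients would disclose or that clinicians would image less. The 720 patients are a ceiling on exposure and do not measure bias.

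**Conclusion.** The point holds as an internal inconsistency of modest expected consequence. The plan hides the imaging focus from patients and clinicians and protects that on the clinician side, but it approaches Study 1 patients for imaging interviews while their outcome is accruing and their clinician may still be enrolling.

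The direct effect is negligible, at 0.8% of patients. The route that matters is disclosure to a clinician who is still enrolling, which could reach up to 17% of clinicians and at most about 16% to 19% of patients. Those figures assume 30 different clinicians and interviews with each one's first enrolee. The direction and size of any resulting bias are unknown. Under the assumed ranges it runs from trivial to 3.6 points in one profession's rate, and the upper end needs an extreme combination. The change is worth making because it is cheap and cannot be made once the interviews have taken place.

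**What to change.** 1. **Scheduling.** Draw interview patients from clinicians who have completed, or are about to complete, Study 1 enrolment. These patients are the clinician's most recent enrolees, so their experience is still fresh, and where dyads are explored the two interviews fall closer together.
2. **Request to interviewees.** Ask them not to discuss the interview content with their clinician.
3. **Sensitivity analysis in Study 1.** Record each interview date, then repeat the imaging rates and regression models without interviewed patients and without any patient enrolled by the same clinician after that date. Truncating the interviewees' follow-up at the interview would be a poor substitute: it gives them a shorter outcome window than everyone else and leaves the clinician's later patients in.

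The scheduling rule closes most of the clinician route but not the interviewee's own 12-month outcome, which is why the third step is needed.

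**Cost.** Patient interviews start later, and the pool for purposive sampling by referral status is smaller. Because enrolment is up to 25 per clinician, staff must track who is near the end; the roughly fortnightly contact with practices already planned should allow this. The sensitivity analysis loses 30 patients and, if the rule is kept, few others.

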### Qualitative data analysis

We will undertake content and thematic analysis of interview transcripts and both the manifest and latent content will be examined [72]. Both clinician and patient datasets will be categorised in relation to consistency with guideline recommendations for imaging. Where possible, we will also explore the perceptions of the patient and clinician as dyads to understand how this interaction may influence imaging decisions. Data will be analysed to identify barriers and facilitators that influence clinicians’ clinical behaviour about imaging for low back pain. Factors will be thematically mapped to the domains of the TDF. Factors emerging on multiple occasions, or considered likely to influence clinical behaviour, will be deemed relevant to identify important theoretical domains. The initial analysis of interview data will be undertaken by a project staff member (with qualitative method expertise), and a random subset of 20% of interviews will be independently coded and analysed by a second researcher (research assistant or graduate student) as verification of the initial analysis. Concordance between coders will be determined and consensus reached. When discrepancies remain, these will be discussed with a senior investigator until agreement is reached.

### Project advisory committee

Our project Advisory Committee comprises all investigators and representatives of the partner organisations. Partner organisations include the Ontario Physiotherapy Association, the Ontario Chiropractic Association and the Ontario College of Family Physicians. The committee meets at least twice each year over the project duration to advise on all aspects of the project.

## Discussion

This will be the first Canadian study to document the extent of the overuse of imaging for low back pain, and the first worldwide to include data from all relevant professions offering primary care for people with low back pain and who can refer for imaging. The outputs will be robust information about rates of inappropriate imaging for low back pain, along with predictors and reasons why inappropriate imaging is occurring. The study will also reveal differences in rates of recommending imaging among types of clinicians, and describe demographics and patterns of care for people with low back pain in primary care settings. Using both quantitative and qualitative results, knowledge translation strategies will be developed to address the issue of inappropriate imaging in these professions. Working with our project partners, the knowledge translation strategies will aim to be relevant, feasible and acceptable for each profession and the general public.

## Abbreviations

CT: Computed tomography
ICES: Institute for Clinical Evaluative Sciences
ICPC-2: International Classification of Primary Care
LBP: Low back pain
MRI: Magnetic resonance imaging
OHIP: Ontario Health Insurance Plan
PET: Positron emission tomography
TDF: Theoretical Domains Framework
